## Abstract

**Background:**

Beach chair positioning during general anesthesia is associated with a high incidence of cerebral desaturation; poor neurological outcome is a growing concern. There are no published data pertaining to changes in cerebral oxygenation seen with increases in the inspired oxygen fraction or end-tidal carbon dioxide in patients anesthetized in the beach chair position. Furthermore, the effect anesthetic agents have has not been thoroughly investigated in this context. We plan to test the hypothesis that changes in inspired oxygen fraction or end-tidal carbon dioxide correlate to a significant change in regional cerebral oxygenation in anesthetized patients in beach chair position. We will also compare the effects that inhaled and intravenous anesthetics have on this process.

**Methods/design:**

This is a prospective within-group study of patients undergoing shoulder arthroscopy in the beach chair position which incorporates a randomized comparison between two anesthetics, approved by the Institutional Review Board of the University of Michigan, Ann Arbor. The primary outcome measure is the change in regional cerebral oxygenation due to sequential changes in oxygenation and ventilation. A sample size of 48 will have greater than 80% power to detect an absolute 4-5% difference in regional cerebral oxygenation caused by changes in ventilation strategy. The secondary outcome is the effect of anesthetic choice on cerebral desaturation in the beach chair position or response to changes in ventilation strategy. Fifty-four patients will be recruited, allowing for drop out, targeting 24 patients in each group randomized to an anesthetic. Regional cerebral oxygenation will be measured using the INVOS 5100C monitor (Covidien, Boulder, CO). Following induction of anesthesia, intubation and positioning, inspired oxygen fraction and minute ventilation will be sequentially adjusted. At each set point, regional cerebral oxygenation will be recorded and venous blood gas analysis performed. The overall statistical analysis will use a repeated measures analysis of variance with Tukey’s HSD procedure for post hoc contrasts.

**Discussion:**

If simple maneuvers of ventilation or anesthetic technique can prevent cerebral hypoxia, patient outcome may be improved. This is the first study to investigate the effects of ventilation strategies on cerebral oxygenation in patients anesthetized in beach chair position.

**Trial registration:**

NCT01535274

## Background

Poor neurological outcome in otherwise healthy patients following anesthesia in the beach chair position is a significant concern
[1] and has been reported in patients with recorded blood pressures that many anesthesiologists would consider acceptable
[2].

There are compelling arguments for the application of a non-invasive monitor of cerebral blood flow, function and/or oxygenation for patients placed in the beach chair position. The measurement of regional cerebral oxygenation (rSO_2_) has been widely used for patients undergoing cardiac
[3] and vascular surgery
[4,5] and, more recently, in anesthetized patients undergoing surgery in beach chair position
[6] where it has revealed a high incidence of severe cerebral desaturation events
[7]. Even patients undergoing arthroscopic shoulder surgery in the beach chair position with regional anesthesia (brachial plexus block) and sedation alone have a 10% chance of experiencing severe cerebral desaturation
[8].

The use of cerebral near-infrared spectroscopy (NIRS) allows for the continuous non-invasive monitoring of rSO_2_ by measuring the relative concentrations of oxyhemoglobin and deoxyhemoglobin within the field of view and, therefore, provides an estimate of the balance between cerebral oxygen supply and demand
[9]. Recent reports in conscious volunteers
[10] and anesthetized patients without vascular disease
[11] demonstrate a relationship between inspired oxygen fraction (FIO_2_) and end-tidal carbon dioxide (PETCO_2_) with cerebral oxygenation.

Observational data suggest a relationship between PETCO_2_ and rSO_2_ specifically in patients anesthetized in the beach chair position
[12] and mechanical ventilation may have negative influence on cerebral auto-regulation
[13]; as one of the primary determinants of set minute ventilation, PETCO_2_ must be considered. Furthermore, different anesthetic agents have distinct effects on cerebral hemodynamics and metabolism
[14,15], yet there has been no direct comparison of the effects of anesthetic agents on rSO_2_ in the beach chair position. The effect on cerebral oxygenation resultant upon any interaction between inspired gas composition and anesthetic choice will be of interest.

The study described here will test the hypothesis that the manipulation of inspired oxygen fraction and end tidal carbon dioxide leads to significant changes in rSO_2_ in patients anesthetized in the beach chair position. The influence of anesthetic technique on this process will be tested as a secondary outcome.

## Methods/design

This is a prospective within-group study with an additional randomized comparison of two anesthetic regimens (Figure
1). The study was approved by the Institutional Review Board of the University of Michigan, Ann Arbor. The primary aim is to determine the effect of increasing the FIO_2_ or PETCO_2_ on cerebral oxygen saturation in patients anesthetized in the beach chair position. Our secondary aim is to investigate the effects of differing anesthetic agents on cerebral oxygenation in patients placed in the beach chair position.

**Figure 1 F1:**
[figure not shown]
Figure illustrating the overall study design.

Patients who are scheduled for elective arthroscopic shoulder surgery in the beach chair position under general anesthesia with supplemental interscalene block will be recruited following written informed consent. All surgeries will be conducted by a single surgeon and single anesthesiologist at a “stand-alone” ambulatory surgery facility. Patients will be excluded if they refuse to give consent, are ineligible for interscalene block, have a history of cardiovascular disease, cerebrovascular disease, hypertension (either by diagnosis, pharmacologic treatment as a surrogate, or a blood pressure measured in the surgical preoperative clinic of greater than 140/90), suffer from respiratory failure, or do not speak English. Recruited patients will undergo computer-generated randomization to receive desflurane or total intravenous anesthesia (TIVA) with propofol for maintenance of anesthesia. These agents were chosen because they have differential effects on cerebral vasodilation, auto-regulation and CO_2_ responsiveness
[15-17]. Patients and data analysts will be blinded to the anesthetic choice; the anesthesiologist caring for the patient will be blinded to cerebral oximetry values. All patients will have an interscalene block placed before induction of anesthesia by a single anesthesiologist. Patients will be pre-medicated with midazolam 0.5-2 mg. Following pre-oxygenation, anesthesia will be induced using fentanyl (1–2 mcg/kg) and propofol (0.5-2 mg/kg). Muscle relaxation will be initiated and maintained with an appropriate combination of succinylcholine and non-depolarizing muscle relaxants as deemed necessary by the anesthesiologist. The patient’s trachea will be intubated and their lungs ventilated. General anesthesia will be maintained as dictated by randomization. Depth of anesthesia will be assessed by Bispectral Index (BIS; Covidien, Boulder, CO) and be controlled within the range 40–60 for all agents. Nitrous oxide could possibly confound results and will therefore not be used.

There may be an advantage of ephedrine over phenylephrine in preserving rSO_2_ when these drugs are used as a bolus for the management of hypotension
[18]. Phenylephrine given by bolus is associated with a 2.8% reduction in rSO_2_ of approximately 8 min duration whereas ephedrine is not associated with any such change
[19]. The relative effect of these agents when used as infusions has not been published and phenylephrine has been used as an infusion in other studies examining rSO_2_. Here, we will use ephedrine (5 mg) in preference to phenylephrine (50-100mcg) as an intravenous bolus medication for the treatment of intraoperative hypotension when heart rate is less than 80 beats per minute. Phenylephrine by infusion (200mcg/ml) will be titrated to maintain blood pressure within 20% of preoperative mean arterial pressure (MAP) when there has been a requirement for more than 400mcg of phenylephrine over a 20 min period. Pre-treatment with ephedrine significantly blunts the decrease in rSO_2_ seen with bolus phenylephrine for at least 20 min
[19]. If phenylephrine bolus dose is used as the first treatment for intraoperative hypotension we will delay the recording of results following a trial intervention by at least 8 min.

For MAPs greater than 70-80 mmHg associated with intraoperative bleeding the initial treatment will be to ensure adequate depth of anesthesia (BIS 40–60), followed by administration of incremental boluses of fentanyl 25mcg, up to a maximum dose of 2.5 mcg/kg. Failure of this to achieve the required reduction in blood pressure will result in the administration of the antihypertensive medications labetolol or hydralazine at the discretion of the patient’s anesthesiologist.

Standard American Society of Anesthesiologists monitoring will be used for all patients. The BIS Quatro electrode will be placed diagonally on the patient’s left forehead. Cerebral oxygenation will be measured using the INVOS 5100C monitor (Covidien, Boulder, CO). Optodes will be applied, before induction of anesthesia, by a single trained researcher on either side of the BIS Quatro sensor as recommended by the manufacturer.

Following induction of anesthesia, FIO_2_ and minute ventilation will be sequentially adjusted to achieve:

1) FIO_2_ 30% (70% nitrogen), PETCO_2_ 30 mmHg – supine position.

2) FIO_2_ 30% (70% nitrogen), PETCO_2_30mmHg – beach chair position.

3) FIO_2_ 100%, PETCO_2_ 30 mmHg – beach chair position.

4) FIO_2_ 100%, PETCO_2_ 45 mmHg – beach chair position.

5) FIO_2_ 30%, PETCO_2_ 30 mmHg – beach chair position.

Minute ventilation will be adjusted by changing respiratory rate rather than manipulating tidal volume. Starting tidal volume will be set at 6–8 cm^3^/kg. The first measurement point in beach chair position will be obtained 15 min after positioning (at which point the maximal decrease in cerebral oxygen saturation is observed to occur
[7]) or immediately if severe cerebral desaturation (absolute value rSO_2_ < 55% or a decrease from baseline of ≥ 20%) is sustained for ≥ 3 min in either hemisphere. It has been shown that the change in rSO_2_ is complete and stable within 5 min following a change in inspired gas composition
[4]. Thus, after 5 min at each subsequent set point, rSO_2_ will be recorded and venous blood gas analysis performed. If a patient’s pulse oximetry reading is persistently <95% at FIO_2_ 30% a higher FIO_2_ will be used at the discretion of the patient’s anesthesiologist, the patient will be withdrawn from the study and an additional patient will be recruited. All sustained cerebral desaturation events, as defined above, will be recorded and communicated to the anesthesiologist to allow intervention as deemed appropriate by the anesthesiologist. Data will be recorded as a “snap-shot” at the time of venous blood gas analysis. A separate intravenous cannula will be placed into a peripheral vein for this purpose. Demographic, intra-operative and outcome data will be retrieved from the patient’s electronic anesthetic and medical records.

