### Statistical considerations

#### Power

The reported mean rSO_2_ is 67.1% ± 6.2 for patients placed in beach chair position
[7]. Based on a previous investigation
[11], we expect a 6–8 percentage point difference in rSO_2_ resultant upon the planned change in FIO_2_ and a 2–4 percentage point difference resultant upon the planned change in PETCO_2_. A total percentage point increase in excess of 10 would be of clinical significance. A sample size of 48 will have a power of greater than 0.8 to detect a 4-5% in the planned pairwise comparisons. Allowing for an approximately 10% drop out 54 subjects will be recruited, targeting 24 patients in each group randomized to an anesthetic. The power for the comparison between the two anesthetic regimens is better than 85% for a difference of 6% which would be a clinically important difference for the secondary outcome.

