#### Analysis

Data will be analyzed with a repeated measures two-way analysis of variance in which ventilation strategy is the within-subjects factor and anesthetic regimen is the between-subjects factor. Residuals will be assessed for normality and equal variances; if necessary, the analyses will be adjusted. The primary analysis will focus on the comparison between the ventilation strategies. A post hoc Tukey’s HSD procedure will be used to correct for all pairwise comparisons between ventilation strategies.

The effect of desflurane or propofol on cerebral desaturation and a possible differential response to changes in ventilation strategy will be evaluated as a secondary outcome measure. Analysis for the primary outcome will be adjusted if interaction effects between ventilation strategy and the anesthetic used are significant. A p value of <0.05 will be considered statistically significant.

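### Withdrawing and replacing randomized patients with low SpO2 at FIO2 30% can bias the secondary desflurane v propofol comparison and leaves it unclear whether 54 is a ceiling

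*Protocol article*

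**What the plan says.** All of this is in the protocol article.

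- **Randomization (Methods/design).** "Recruited patients will undergo computer-generated randomization to receive desflurane or total intravenous anesthesia (TIVA) with propofol for maintenance of anesthesia".
- **Timing (Methods/design, list of set points).** "Following induction of anesthesia, FIO_2_ and minute ventilation will be sequentially adjusted to achieve" five set points. FIO2 30% applies at set points 1 (supine), 2 and 5 (beach chair).
- **Trigger and consequence (Methods/design, measurement paragraph after the list).** If the "pulse oximetry reading is persistently <95% at FIO_2_ 30"%, the anesthesiologist may use a higher FIO2, "the patient will be withdrawn from the study and an additional patient will be recruited".
- **Blinding (Methods/design).** "Patients and data analysts will be blinded to the anesthetic choice; the anesthesiologist caring for the patient will be blinded to cerebral oximetry values".
- **Sample size (Power).** "Allowing for an approximately 10% drop out 54 subjects will be recruited", with a target of 24 per anesthetic arm.
- **Secondary outcome (Analysis).** "The effect of desflurane or propofol on cerebral desaturation", together with any difference between agents in the response to ventilation changes, within a repeated measures two-way analysis of variance. The section does not mention the withdrawn patients.

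**The concern.** A randomized comparison is protected only while patients are analyzed in the groups to which they were allocated. Here a patient leaves the study because of something observed after allocation and after exposure to the assigned agent. Three features make this more than a formality.

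1. **The trigger is close to the outcome.** Low arterial saturation bears on cerebral oxygenation, which is what the trial measures. The Discussion itself cites more frequent cerebral desaturation with propofol TIVA than with inhalational anesthesia during one-lung ventilation. By the article's own reasoning, compromised oxygenation is a setting in which the arms might differ.
2. **The trigger leaves room for judgment.** No duration defines a persistent reading, although the same paragraph sets 3 minutes for a sustained cerebral desaturation. The person who calls it is blinded to cerebral oximetry values but is not stated to be blinded to the agent.
3. **Replacement restores the number but not the comparison.** A replacement is subject to the same rule, so each arm fills up with patients who tolerate FIO2 30% under that agent.

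At stake are the between-arm difference in rSO2 and, more so, the between-arm comparison of desaturation events. There is also a planning question: the 54 already include an allowance for loss, and the replacement rule adds further patients without saying where recruitment ends.

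**Working it through.** **Inputs from the article.** SD of rSO2 6.2 points; 48 evaluable, 24 per arm; about 10% dropout; 54 recruited; power better than 85% for a 6-point anesthetic difference; significance level 0.05 (taken as two-sided, which is not stated).

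**Inputs assumed.** Withdrawal rate by arm and the SpO2-rSO2 correlation r. The article gives neither, so ranges are shown.

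**Step 1: the plan's own figures.**
- Recruitment: 48/(1 − 0.10) = 53.3, rounded up to 54. This covers 54 − 48 = 6 losses (6/54 = 11.1%).
- Anesthetic comparison: standardized difference 6/6.2 = 0.97. Two-sample t-test power at 24 per arm is 0.907, which agrees with the stated lower bound of 85%.
- With fewer patients per arm, power is 0.880 at 22 and 0.847 at 20. Replacement therefore does little to protect power for this comparison; it falls just under the stated 85% only at about 20 per arm.

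**Step 2: order of events.** Randomization, induction and assigned maintenance agent, FIO2 30% at set point 1, 2 or 5, low SpO2, withdrawal, replacement. The exclusion always follows allocation and exposure. A patient who meets the trigger at set point 5 may already have readings at set points 1 to 4.

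**Step 3: possible shift in mean rSO2.** Treat SpO2 and rSO2 as bivariate normal and remove the lowest fraction p of SpO2 in each arm. With φ the normal density and z_p the normal quantile:

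shift = 6.2 × r × [φ(z_p1)/(1 − p1) − φ(z_p2)/(1 − p2)]

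For p = 0.10, φ(z)/(1 − p) = 0.1755/0.90 = 0.195. For p = 0.05 it is 0.1031/0.95 = 0.109.

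| Withdrawn, arm A v arm B | r = 0.2 | r = 0.5 | r = 1 |
|---|---|---|---|
| 10% v 0% | 0.24 | 0.60 | 1.21 |
| 5% v 0% | 0.13 | 0.34 | 0.67 |
| 10% v 5% | 0.11 | 0.27 | 0.54 |
| 5% v 5% | 0 | 0 | 0 |

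The standard error of the difference is 6.2 × √(2/24) = 1.79. A shift of 0.60 is 0.60/1.79 = 0.34 standard errors and takes a nominal 5% two-sided error to about 6.3%. A shift of 1.2 takes it to about 10.3%.

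**Step 4: possible shift in event proportions.** Assume equal true risk, 8/27 (29.6%) in each arm, and three withdrawals in all.

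| Withdrawals | Observed | Difference |
|---|---|---|
| 3 v 0, all three with events | 5/24 (20.8%) v 8/27 (29.6%) | 8.8 points |
| 2 v 1, all three with events | 6/25 (24.0%) v 7/26 (26.9%) | 2.9 points |
| 3 v 0, one with an event | 7/24 (29.2%) v 8/27 (29.6%) | 0.5 points |

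If replacements carry the same risk as the patients retained, these proportions do not change on average.

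**Step 5: primary comparison.** Each patient is their own control across set points. A patient who cannot be held at FIO2 30% at set point 1 or 2 has no complete protocol-defined FIO2 contrast to contribute. The loss is then one of reach: the estimated FIO2 effect describes patients who tolerate 30%.

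**The case against.** The strongest reply has five parts.

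- **Bias is not shown.** It needs withdrawal, or the outcomes of those withdrawn, to differ by arm, and the article gives no rate of low SpO2 in either. With equal withdrawal the model above gives no shift. Patients with respiratory failure, cardiovascular disease or cerebrovascular disease are excluded at entry, so frequent triggering should not be presumed. This stands: the claim can only be that the rule *can* bias the comparison.
- **The contrast is secondary and the likely shift is small.** This also stands and limits the weight of the point.
- **The article does not say that earlier readings are discarded, and handling of partial data commonly belongs in an analysis plan that is not shown.** This is partly right. How partial data are modelled may well be set out elsewhere. But withdrawal from the study with replacement is a rule the article itself states, and nothing in its Analysis section returns these patients to the randomized comparison. The article also undertakes to record all sustained cerebral desaturation events, which fits poorly with removing some patients from the study.
- **A general dropout allowance and replacement for one named cause can coexist.** Correct. A reader might infer that the loss is counted twice, but the article does not show that. What remains is that it does not say whether 54 is a ceiling.
- **Little may be recoverable.** Readings after FIO2 is raised belong to no protocol set point. This is true, and it limits the gain from the fix without removing it.

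A reader might also infer that the rule removes the patients most likely to respond to oxygen. Nothing in the article links SpO2 below 95% to a larger rSO2 response, so that is not claimed.

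**Conclusion.** The point holds in limited form. The article states a post-randomization, oxygenation-related exclusion with replacement, called by an anesthesiologist not stated to be blinded to the agent. It can bias the secondary anesthetic comparison if withdrawals or their outcomes differ by arm.

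The size cannot be fixed from the article. Under assumed correlations of 0.2 to 0.5 and withdrawal of up to 10% v 0%, the shift in mean rSO2 is about 0.1 to 0.6 points, and 1.2 at correlation 1, against 6 points of interest. Event proportions are more fragile. A reader might take the near 9-point difference in Step 4 as the expected distortion, but it is a one-sided assumed case, and other splits of the same three withdrawals give 2.9 or 0.5 points.

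For the primary within-patient comparison the consequence is mainly narrower generalizability. The planned sample size and power reproduce and are not in question; only the status of 54 as a ceiling needs settling. The change is worth making because it is cheap and leaves patient care as it is.

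**What to change.** Leave the clinical decision on FIO2 exactly as it is and change only the handling of the data:

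1. State that such a patient stops the ventilation sequence, rather than being withdrawn from the study.
2. Keep all readings taken at protocol set points and analyze them by randomized arm in a mixed model, which accepts incomplete sequences.
3. Keep the patient in the denominator for cerebral desaturation events.
4. Report the number of these cases by arm.
5. Show completers plus replacements only as a sensitivity analysis.
6. Reconcile Methods/design with Power: say whether 54 is a ceiling. If replacements are kept, give each the next allocation on the randomization list and keep the replaced patient in the analysis.

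The cost is a change of wording, a mixed model in place of the repeated measures analysis of variance, and a few patients with partial data. The mixed model relies on the missing readings being explained by the data it uses. Because stopping is tied to oxygenation, that assumption should be acknowledged when the anesthetic comparison is reported.

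### A short steady-state mean of rSO2 at each set point would be at least as precise as the planned single snap-shot, at little cost; the gain is of unknown size

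*Protocol article*

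**What the plan says.** All references are to the protocol article.

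- **Outcome** (Abstract, Methods/design): "The primary outcome measure is the change in regional cerebral oxygenation due to sequential changes in oxygenation and ventilation".
- **Timing** (Methods/design, after the list of five set points): the first beach chair reading is taken 15 minutes after positioning, or at once if severe desaturation persists. Then: "Thus, after 5 min at each subsequent set point, rSO_2_ will be recorded and venous blood gas analysis performed".
- **Form of the reading** (same paragraph): "Data will be recorded as a “snap-shot” at the time of venous blood gas analysis". No averaging window or repeat reading is mentioned.
- **Reason for the timing** (same paragraph): "It has been shown that the change in rSO_2_ is complete and stable within 5 min following a change in inspired gas composition".
- **Nature of the monitor** (Background): near-infrared spectroscopy "allows for the continuous non-invasive monitoring of rSO_2". The severe-desaturation rule in Methods/design applies when the fall "is sustained for ≥ 3 min in either hemisphere", which can only be judged by following the reading over time.
- **Planning figures** (Statistical considerations, Power): "The reported mean rSO_2_ is 67.1% ± 6.2 for patients placed in beach chair position". Expected effects are 6–8 points for FIO2 and 2–4 points for PETCO2. With 48 patients, power above 0.8 is claimed for 4–5 points.

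**The concern.** A reading at one moment is the patient's plateau value at that set point plus whatever fluctuation is present at that instant. The primary outcome subtracts one such reading from another, so the fluctuation variance is counted twice in each contrast. The protocol's stability argument supports when to measure. It does not require measuring only once: if rSO2 is on a plateau, the mean over a short stretch of that plateau estimates the same quantity.

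What is at stake is precision for the PETCO2 step (set point 3 to set point 4), one of the two manipulations in the primary aim. Its expected effect lies at or below the difference that the trial says it can detect. The FIO2 step is expected to be large enough not to need the help.

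**Working it through.** **1. Inputs.** From the documents: SD 6.2, N = 48, 24 per arm, five set points, Tukey's HSD for all pairwise comparisons, alpha 0.05 (taken as two-sided). Not in the documents, and therefore assumed:
- the within-patient correlation ρ between set points;
- the momentary noise SD s;
- the number m of effectively independent readings in the averaging window.

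**2. The plan's own power, with single readings.**
- Between arms: 6 points, SD 6.2, 24 per arm. The standardised effect is 6 / (6.2 × √(2/24)) = 3.35. Power is 0.918 (normal) or 0.907 (t), which meets the stated figure of better than 85%.
- Pairwise: SD of the difference = 6.2 × √(2(1 − ρ)). The Tukey critical value for five set points is 2.755.
  - At ρ = 0 (SD 8.77), power is 0.657 at 4 points and 0.882 at 5. It reaches 80% at about 4.6 points, inside the stated 4–5.
  - At ρ = 0.3 (SD 7.34), power is 0.845 at 4 points and 0.974 at 5.

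The claim is therefore reproduced without any averaging.

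**3. Effect of averaging.** The mean of several equally variable readings never has a larger variance than one of them. Replacing each snap-shot by a mean worth m independent readings lowers the variance of a difference by 2s²(1 − 1/m).

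At ρ = 0.5 the snap-shot variance is 6.2² = 38.44. For example, with s = 2 and m = 3 it becomes 38.44 − 2 × 4 × (2/3) = 33.11, an SD of 5.75. The interval narrows by 1 − 5.75/6.2 = 7%.

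Power for a 3-point effect (N = 48, noncentral t, critical value 2.755):

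| Noise SD s | m | SD of difference | CI narrower by | Power |
|---|---|---|---|---|
| any | 1 | 6.20 | 0% | 0.72 |
| 1 | 3 to 6 | 6.09 to 6.06 | about 2% | 0.74 to 0.75 |
| 2 | 3 to 6 | 5.75 to 5.64 | 7 to 9% | 0.80 to 0.82 |
| 3 | 3 to 6 | 5.14 to 4.84 | 17 to 22% | 0.90 to 0.94 |

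The first row is the case of successive readings that are almost perfectly correlated: no gain, and no loss.

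**4. Dependence on ρ.**
- At ρ = 0, snap-shot power for 3 points is 0.35, and averaging with s = 2 raises it only to about 0.39.
- At ρ = 0.7, power for 3 points is already 0.94. For 2 points it rises from 0.55 to 0.70–0.75 with s = 2.

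**5. Plausibility of the top row.** At ρ = 0.5 the variance per reading that enters a difference is 38.44 / 2 = 19.2. A noise SD of 3 makes fast noise 9 / 19.2 = 47% of it; SD 2 makes it 21% and SD 1 makes it 5%. Nothing in the documents says which is nearer the truth.

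**6. Where the window can go.** The protocol asserts stability within 5 minutes and records after 5 minutes. A 60-second window ending at a sample drawn at 5 minutes would cover minutes 4 to 5, before stability is assured. A response still settling would then be pulled toward the previous set point. The cited stability also concerns inspired gas composition; none is cited for the PETCO2 step. The window should therefore start at the 5-minute mark, not end there.

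**The case against.** The strongest case against is that the benefit is wholly assumed. The documents give no noise SD, autocorrelation or within-patient correlation, and do not say how far the displayed value is already smoothed. If it is smoothed, m is close to 1 and the gain is nil. The only transient that the protocol quantifies is the 2.8% fall lasting about 8 minutes after a phenylephrine bolus. A 60-second mean would not remove that, and the protocol already delays recording for it when such a bolus is the first treatment. The power argument also joins two settings: a detectable difference of 4–5 points corresponds to ρ near 0, whereas at ρ = 0.5 single readings already detect 3.2 points with 80% power. All of this stands and limits the size of the point. It does not make the snap-shot preferable on precision.

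Three stronger readings are tempting and not supported:

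- *The trial discards precision that it already collects.* The technique is continuous and the 3-minute rule needs watching, but nowhere is the trace said to be stored for analysis.
- *The person recording rSO2 is not listed as blinded, so the choice of instant may bias the result.* The reading is tied to the blood gas at a set time, and a window anchored to the same sample would leave the same discretion over when to sample.
- *The trial is undersized because of the snap-shot.* The stated power is reproduced with single readings.

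**Conclusion.** The point holds as a minor, low-cost design improvement. The protocol explicitly chooses one momentary value per set point, and a short mean on the plateau would be at least as precise. The benefit falls mainly on the 2–4 point PETCO2 contrast. Its size cannot be derived from the documents: for a 3-point effect at ρ = 0.5 it ranges from no change at 0.72 to 0.94 under the most favourable assumption shown. The conclusion that averaging does no harm rests on the window lying wholly on the plateau. There is no contradiction in the document here and no fault in the sample size.

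**What to change.** 1. Confirm that the monitor trend is saved with time stamps, and time-stamp each blood sample.
2. Define rSO2 at each set point as the mean of the stored readings over a fixed 60-second window, with the blood sample drawn at its end so that the two stay paired.
3. Start the window no earlier than the 5-minute mark. For the first beach chair point, start it at 15 minutes, or when the early-desaturation rule triggers. This defines the measurement only; it should not change when a desaturation event is communicated or acted on.
4. Use the same window at every set point, including the supine one.
5. Keep the snap-shot value as a sensitivity analysis.

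Cost: about one extra minute per set point, so roughly five minutes per patient over five set points, and slightly more data handling. No extra patients, procedures or staff are needed. If the trend turns out not to be saved, arranging its capture comes first.
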